### 2.4. Study Locations

Eligible facilities will be determined based on whether they provide training for cardiovascular specialists certified by the Japanese Circulation Society, and their regional characteristics. The centers for this study will be hospitals or clinics that provide both inpatient and outpatient care for patients with chronic heart failure (HF). They must meet the following criteria:
They must employ one or more nurses with expertise in chronic disease nursing, and who is certified as a specialist in chronic HF nursing or as an HF nurse.They must be able to establish a system for providing both in-person and telephone-based support for chronic HF patients in the outpatient setting, led by certified HF nurses or nurses with more than 3 years of experience in HF nursing.

Potential intervention participants who meet the selection criteria for participation in the study will receive both written and oral explanations of the purpose and content of the study from the collaborating research institution. Patients who express interest in participating will be asked to sign a consent form. Once practitioners are identified and recruited, informed consent (Supplemental Material: Agreement form) will be obtained immediately.

### 2.5. Randomization and Blinding

Eligible facilities will be gathered through open solicitation. The joint research institutions will be selected based on discussions among and comprehensive review by the internal meetings of this association. We will assign the intervention group (facility) and the control group (facility) at a 1:1 ratio through stratified randomization according to the volume of potential patients. Patients from each facility who provide their consent will be included as intervention subjects. Since the study involves a behavioral intervention without a potential placebo counterpart, it will be impossible to blind both investigators and participants to group allocations. However, data collection research assistants will be trained on consistent administration of measures and awareness of biases.

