## Abstract

Background: Heart Failure (HF) is a common chronic disease that has a high readmission rate and is associated with worsening symptoms and major financial impacts. Disease management implemented during or after an HF hospitalization has been shown to reduce hospitalization and mortality rates. Particularly for outpatients, it is necessary to provide self-care interventions. Structured nurse-led support such as timely follow-ups, including phone calls, is beneficial for improving self-care assessments. Evidence for nurse-led support has been investigated but is less than conclusive. The aim of this study is to compare the effectiveness of a nurse-led structured intervention for outpatients with chronic HF against the usual medical care in terms of self-care behaviors and occurrence of symptom exacerbation or rehospitalization. Methods and analysis: This is a cluster-randomized controlled trial. A total of 40 facilities with certified HF nurses will be allocated to two-arm clusters at a 1:1 ratio, randomly to the intervention or usual care arms. A total of 210 participants will be assigned from the hospital. Participants will be adults aged 18 years or older diagnosed with chronic HF who are classified as Stage C according to the ACCF/AHA Heart Failure staging system. In the intervention group, patients will receive structured nursing support. This begins with weekly support, including phone calls, for the first month, then transitions to monthly support thereafter. The aim is to ensure the stability of their living conditions, promote medication adherence, and encourage self-management. In the control group, patients will receive the usual care. Primary outcomes will assess the improvement or continuation of self-care behavior as measured by changes in EHFScBS (European Heart Failure Self-Care Behavior Scale) scores. Secondary outcomes include occurrence of readmission within 30 days, 3 months, 6 months, and 1 year after discharge, duration of home care until readmission, and blood levels of BNP and NT-proBNP.

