### 2.3. Sample Size

A sample size of 210 (105 in each arm) will allow us to detect a difference of four units in the EHFScBS scores with 80% statistical power. Assumptions are based upon data from the CHART-2 study, which estimated a mean clinical estimated difference of 4 in the EHFScBS before and after intervention, with a standard deviation of 8.5 [15,16]. The ICC was 0.05, and a dropout rate of 30% due to mortality or other reasons over one year was assumed, based on previous research results, in order to determine the sample size [17,18].

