## 8. Statistical Method

The Japan Nursing Association will submit the data received from the intervention and control groups’ medical institutions to a contracted data analysis organization for analysis. The between-group comparison of the change in self-care behavior continuity and changes in BNP and NT-proBNP in the baseline values at discharge and changes after intervention (1 and 3 months later) will be performed. The Spearman rank correlation coefficient will be used to measure the relationship between the scores of cardiac functions and the EHFScBS. The Mann–Whitney U-test will be used to compare the scores of the EHFScBS between the two groups with respect to patient backgrounds. The McNemar test will be used to analyze the changes in the two groups’ readmission and symptom deterioration rates, with the corresponding t-test employed for frequency, relative risk, and absolute risk reduction for risk difference. The presence or absence of readmission and the time to readmission between the intervention and control groups will be analyzed by the Kaplan–Meier method and tested for significance using the log-rank test. The Cox proportional hazard model and propensity score analysis will be used to compare between-group differences. Multiple imputation techniques will be employed to handle missing data, ensuring robustness and reducing bias in the findings. In the above analysis for the comparison, covariate adjustment from the baseline patient characteristics will be applied to gain efficiency in the estimation for the treatment effect, when it is necessary.

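### Facilities are randomised within patient-volume strata, but Section 8 uses that stratum in no between-arm analysis; once clustering is handled, this costs a small amount of precision

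*Protocol article*

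**What the plan says.** The facility is the unit of randomisation: "A total of 40 facilities with certified HF nurses will be allocated to two-arm clusters at a 1:1 ratio" (Abstract). Section 2.5 adds that facilities are allocated "at a 1:1 ratio through stratified randomization according to the volume of potential patients". The number of strata and their cut-points are not given.

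Section 8 (Statistical Method) lists the analyses. For the self-care scale, "The Mann–Whitney U-test will be used to compare the scores of the EHFScBS between the two groups with respect to patient backgrounds". Readmission and time to readmission "will be analyzed by the Kaplan–Meier method and tested for significance using the log-rank test". A Cox model and a propensity score analysis are also named for comparing the arms. None of these is described as stratified, and none has a stratum or facility term. On adjustment, Section 8 says that "covariate adjustment from the baseline patient characteristics will be applied to gain efficiency in the estimation for the treatment effect, when it is necessary". Facility volume is not among the baseline items listed in Section 6.

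**The concern.** Stratified allocation balances the volume strata between arms, so differences between strata no longer contribute to the variance of the treatment contrast. An analysis that omits the stratum still counts those differences as error. If volume is related to self-care or readmission, a facility-level or mixed-model analysis without the stratum reports intervals that are too wide and tests below the nominal level, and the precision gained by design is not used.

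Section 8 does address adjustment, and its rule does not reach this factor. The rule covers patient characteristics, whereas volume is a facility-level design factor. It is also conditional, whereas a randomisation stratum is fixed in advance and needs no later judgement of necessity. An analysis plan that followed the sentence literally would leave the stratum out.

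**Working it through.** **Inputs.** From Section 2.3: "A sample size of 210 (105 in each arm) will allow us to detect a difference of four units in the EHFScBS scores", at 80% power; "a mean clinical estimated difference of 4 in the EHFScBS before and after intervention, with a standard deviation of 8.5"; "The ICC was 0.05, and a dropout rate of 30% due to mortality or other reasons over one year was assumed". From the Abstract: 40 facilities, 20 per arm. The significance level is not stated, so two-sided 5% is assumed. The share f of between-facility variance explained by the volume stratum is not given, so it is varied from 0 to 1.

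**The plan's own figure.** A difference of 4 with SD 8.5 needs 71 patients per arm before inflation. With 210/40 = 5.25 patients per facility, the design effect is 1 + 4.25 × 0.05 = 1.2125, and dividing by 0.70 gives 123 per arm. With 3.675 completers per facility, the design effect is 1.134 and the result is 116 per arm. Neither matches 105. That mismatch is a separate matter and is not evidence here; it means only that the power figures below start under 80%.

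**Variance components.** Completers: 210 × 0.70 = 147, so m = 147/40 = 3.675 per facility. Between-facility variance: 0.05 × 8.5² = 3.6125. Within-facility variance: 0.95 × 8.5² = 68.6375, or 68.6375/3.675 = 18.677 per facility mean.

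**Facility-level analysis.** With strata balanced by arm, the true variance of the arm difference is 2 × [3.6125 × (1 − f) + 18.677]/20. An analysis without the stratum estimates 2 × [3.6125 + 18.677]/20 = 2.229, an SE of 1.493, whatever f is. Write SE₀ = 1.493 and SE_f for the true value, and use the normal approximation:

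- type I error without the stratum = 2 × [1 − Φ(1.96 × SE₀/SE_f)]
- power without the stratum = Φ((4 − 1.96 × SE₀)/SE_f)
- power with the stratum = Φ(4/SE_f − 1.96)

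| f | True SE | SE overstated by | Type I error, stratum omitted | Power, omitted | Power, included |
|---|---|---|---|---|---|
| 0 | 1.493 | 0% | 5.0% | 76.4% | 76.4% |
| 0.10 | 1.481 | 0.8% | 4.8% | 76.6% | 77.1% |
| 0.25 | 1.462 | 2.1% | 4.5% | 76.9% | 78.1% |
| 0.50 | 1.431 | 4.3% | 4.1% | 77.3% | 79.8% |
| 1 | 1.367 | 9.2% | 3.2% | 78.4% | 83.3% |

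A simulation of t-tests on 40 facility means (20,000 runs, two equal strata balanced by arm, equal facility sizes) agrees. Without the stratum, type I error is 4.5%, 4.2% and 3.1% at f = 0.25, 0.5 and 1. Power with and without the stratum is 76% and 75%, 78% and 75%, and 81% and 76%.

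**Patient-level analysis, with no facility term, as listed.** The reported SE is 8.5 × √(2/73.5) = 1.402, against true values of 1.493, 1.462 and 1.431 at f = 0, 0.25 and 0.5. Type I error is then about 6.6%, 6.0% and 5.5%. It falls below 5% only when 3.675 × (1 − f) < 1, that is, f above about 0.73. Adding the stratum but still ignoring clustering reduces the reported SE by the factor √(1 − 0.05f), and type I error becomes about 6.2% at f = 0.25 and 5.8% at f = 0.5, slightly worse than without it.

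The documents give no readmission ICC or event rate, so no size is computed for the readmission analyses.

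**The case against.** The strongest objection is that this rests on silence. Whether a stratification factor enters a model is often left to the analysis plan, which is not shown. Section 8 does not say that patient characteristics are the only permitted covariates, and the qualifier on the Mann–Whitney sentence leaves unclear whether that test is the primary arm comparison. This stands in part: the article does not exclude the stratum, and a reader who infers that it forbids it goes too far. But Section 8 does state an adjustment rule, with a source, a purpose and a condition, and that rule as worded misses a factor the design has already fixed.

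A second objection is that the harm runs the other way for the tests as listed. This stands. With no facility term, intervals are too narrow unless volume explains more than about 73% of between-facility variance. The claim of over-wide intervals holds only once clustering is allowed for.

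A third is that the premise is assumed. Section 2.5 gives no reason for stratifying by volume; balancing patient numbers between arms would be one. If volume does not predict outcome, nothing is lost. This also stands, and is why a range is shown.

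**Conclusion.** The point holds as a small, conditional loss of precision. Given an analysis that allows for clustering, omitting the stratum overstates the SE by about 2%, 4% or at most 9%, and costs about 1, 2.5 or at most 5 points of power, if volume explains 25%, 50% or 100% of between-facility variance. The last case is a ceiling, not an expectation. The figures assume two-sided 5%, equal facility sizes, strata balanced by arm, and the plan's ICC and dropout.

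Three stronger readings are not supported. First, omitting the stratum does not bias the treatment estimate. Second, it does not itself inflate type I error; the inflation in the tests as listed comes from the missing facility term. Third, a reader might compare 83.3% with 76.4% and infer a gain near 7 points. The second figure belongs to f = 0; at f = 1 the analysis without the stratum already has 78.4% power, because the balanced design has removed the stratum variance from the contrast. Low priority, best settled in the same statement that deals with clustering.

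**What to change.** State in Section 8 that every between-arm comparison includes the randomisation stratum (facility patient volume) as a prespecified factor, unconditionally, together with an allowance for facility clustering:

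- For EHFScBS, use a mixed or facility-level model with the volume stratum as a fixed effect.
- For readmission, use a Cox model stratified by volume, with facility-robust standard errors or a facility frailty, and a log-rank test that is both stratified and allows for clustering.

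The condition on necessity can remain for other patient-level covariates, but should not apply to the stratum.

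The cost is a sentence or two of text and no new data, since each facility's stratum is known at randomisation. Statistically it takes one of 38 facility-level degrees of freedom with two strata, or two with three. Even if volume explains nothing, two degrees of freedom move t-based power only from 74.2% to 74.1%.

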### 2.7. Inclusion Criteria

Patients must have had one or more hospitalizations due to HF in the year preceding the index admission. Additionally, they must exhibit one or more of the following adherence-related issues:Living aloneDeterioration in familial support structuresMental health concerns, including depressionCognitive impairmentComplex medication regimens and instructionsExperiencing adverse drug reactions or side effectsInsufficient comprehension of medication regimenInadequate understanding of the disease process and prognosisChallenges in managing medication administration, weight monitoring, and fluid balanceMissing scheduled appointments (no-shows)

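### Patients are probably recruited with the facility's arm known, partly on judgement-based criteria, yet baseline adjustment of the primary EHFScBS comparison is left conditional

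*Protocol article*

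**What the plan says.** - **Allocation.** The Abstract states: "A total of 40 facilities with certified HF nurses will be allocated to two-arm clusters at a 1:1 ratio". Section 2.5 assigns facilities "at a 1:1 ratio through stratified randomization according to the volume of potential patients", says that neither investigators nor participants can be blinded, and names one safeguard: training the data collectors in consistent administration and awareness of bias.
- **Entry of patients.** The next step in Section 2.5 is: "Patients from each facility who provide their consent will be included as intervention subjects". Section 2.4 says: "Potential intervention participants who meet the selection criteria for participation in the study will receive both written and oral explanations". These explanations come from the participating institution.
- **Eligibility.** Section 2.7 requires a heart failure hospitalisation in the year before the index admission and adds that "they must exhibit one or more of the following adherence-related issues". Ten issues follow. Section 2.8 excludes patients whose understanding or judgement is too impaired for consent, with no cut-off.
- **Analysis.** Section 8 compares change from baseline between groups and says that "covariate adjustment from the baseline patient characteristics will be applied to gain efficiency in the estimation for the treatment effect, when it is necessary". It also names a propensity score analysis, in the same sentence as the Cox model.
- **Baseline data.** Section 6 collects EHFScBS and a long list of clinical, cognitive, mood and social items before the intervention.

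**The concern.** Randomising facilities balances the facilities. It does not balance the patients who enter later if those who recruit, or those who are asked, already know the arm. A nurse at an intervention site may favour patients who seem likely to respond, or those who most need help. Patients who dislike telephone contact have a reason to decline only in the intervention arm. With 210 patients over 40 facilities, each site enrols about five (210/40 = 5.25), so a site with more eligible patients than that has room to choose.

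The primary outcome is a self-care behaviour scale, which plausibly depends on motivation and on the starting level. Unequal selection could bias the between-arm difference in either direction. Adjustment for the baseline score is the plain defence against the measured part of such bias, and the stated text leaves it optional, with no trigger given.

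**Working it through.** **1. Is the arm known at recruitment?** The article nowhere says that consent follows randomisation. Four pieces of text point that way: the order of the text in Section 2.5; the wording of Section 2.4, which addresses potential intervention participants; enrolment around an index admission at facilities allocated as whole units (Section 2.7); and the statement that blinding is impossible. No arm-blind recruiter and no patient list drawn up before allocation is described. Recruitment with the arm known is the natural reading, but it remains an inference.

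**2. How much discretion is there?** The prior hospitalisation, living alone and missed appointments are objective. Weaker family support, insufficient grasp of the regimen and inadequate understanding of the disease have no instrument or threshold. Cognitive impairment counts towards inclusion while impaired understanding excludes, so borderline cases can go either way. Discretion is wide but not total.

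**3. What would a baseline gap do?** The plan gives no figure on this point, so this is an illustration. Assumptions:

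- The intervention arm starts d units worse (higher) on EHFScBS, with d from 1 to 3.
- The correlation r between baseline and follow-up is 0.3 to 0.7.
- Selection acts on the observed score, and both arms regress to a common mean.
- There is no treatment effect.

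The expected gap at follow-up is then r × d, and the spurious difference in change is (1 − r) × d, in favour of the intervention:

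| d | r = 0.3 | r = 0.5 | r = 0.7 |
|---|---|---|---|
| 1 | 0.7 | 0.5 | 0.3 |
| 2 | 1.4 | 1.0 | 0.6 |
| 3 | 2.1 | 1.5 | 0.9 |

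The range of 0.3 to 2.1 units is about 8% to 53% of the 4-unit target (0.3/4 and 2.1/4). An unadjusted comparison of follow-up scores would be off by r × d, also 0.3 to 2.1 units, but in favour of control. Under these assumptions, the same imbalance favours a different arm depending on which unadjusted analysis is used.

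**4. What does that do to the error rate?** Inputs from Section 2.3: SD 8.5, ICC 0.05, 105 per arm, 30% dropout over one year. A two-sided 5% test is assumed.

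- With dropout: 105 × 0.7 = 73.5 per arm and 5.25 × 0.7 = 3.675 per facility. The design effect is 1 + 2.675 × 0.05 = 1.134, and SE = 8.5 × √(2 × 1.134/73.5) = 1.49.
- Without dropout: the design effect is 1 + 4.25 × 0.05 = 1.2125, and SE = 8.5 × √(2 × 1.2125/105) = 1.29.

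The false-positive rate for a bias b is 1 − Φ(1.96 − b/SE) + Φ(−1.96 − b/SE):

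| b (units) | SE 1.49 | SE 1.29 |
|---|---|---|
| 0 | 5% | 5% |
| 0.5 | 6% | 7% |
| 1 | 10% | 12% |
| 2 | 27% | 34% |

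The SE is held fixed here, although the SD of a change score itself depends on r. The table therefore gives orders of magnitude only.

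**The case against.** Several points on the other side stand.

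- **Section 8 does not adjust for efficiency alone.** It also plans a propensity score analysis, which is a tool against imbalance. But that analysis sits with the Cox model, and nothing ties it to EHFScBS.
- **A reader might infer that the trial could not show unequal recruitment.** The documents do not support that. Section 6 records baseline self-care, family structure, depression and cognition, so a gap in these would be visible. Only selection on unrecorded traits, or refusal in one arm, would stay hidden.
- **A reader might take the lead quote as proof that consent follows allocation, or that every patient is an intervention patient.** It shows neither. It says nothing about timing, and Section 2.6 includes control patients, so the term used for them is loose wording.
- **Screening procedures and the content of the information sheet commonly belong in the full protocol.** Their absence from an article is no fault, and the supplemental agreement form cannot be seen. The conditional adjustment is different: it is stated text.
- **The size rests on assumptions.** If the arms enrolled patients with stably different self-care levels, each would regress to its own mean. The change comparison then need not be biased, and baseline adjustment could itself introduce bias (Lord's paradox). Adjustment is a sound default, but not a cure for every form of selection.

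**Conclusion.** The concern holds in a limited form. Unblinded cluster recruitment on partly subjective criteria creates a real risk that the arms differ from the start. That the arm is known at consent is well supported by the text, but it is an inference. The documents do not show that unequal selection will occur, nor in which direction.

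The firm defect is in Section 8: adjustment is conditional, its purpose is given as efficiency, and the one method aimed at imbalance is not linked to the primary outcome. The illustrated shift of 0.3 to 2.1 units depends on an assumed gap, an assumed correlation and selection on the observed score. The case for fixing the adjustment in advance does not depend on those values.

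**What to change.** **Section 8.** Drop the condition at the end of the adjustment sentence. State one primary EHFScBS model that accounts for clustering by facility and always adjusts for baseline EHFScBS and the facility-volume stratum. This costs nothing in data: the score is already collected at baseline and the stratum is already used in the randomisation.

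**Section 2.5, where feasible.** Confirm eligibility and complete the baseline EHFScBS before the patient is told the facility's arm. Count eligible, approached and consented patients by arm, so that differential refusal can be seen. The cost is a little screening paperwork at each site.

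**Limits.** Delaying disclosure protects the patient's answers and the baseline score; recruiting staff may still know the arm. Adjustment removes only measured imbalance. Selection on motivation or other unrecorded traits would remain, and the counts by arm help a reader judge how likely it is.
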